## C.4 Participants screening and enrolment

### C.4.1 Initial screening

Participants will be recruited from Mulago and St Joseph ANC clinics. Midwives/counselors or research assistants will approach pregnant women who have tested HIV-negative and determine whether the women came and intend to continue attending as an individual or with their partner. The staff will briefly inform individual women or couples verbally about the study and its requirements and hand them a printed sheet with the same information. Women and couples agreeable to screening for participation will be referred to the study team. During screening, a study clinician, counselor or research assistant will first assess the woman’s provisional eligibility criteria. If the provisional eligibility criteria are met, women will be asked to provide written consent. Once consented, index women will be retested for HIV and if confirmed HIV-negative, will be assessed for final eligibility. At this point, partners of eligible women intending to join the study as couples will be assessed for eligibility and consented if eligible. Enrolled women/couples will be given an appointment to return within the next 2 weeks to complete baseline exams, tests and procedures. All discussions, interviews and examinations will be done in the appropriate language of participants.

| C.4.2 Inclusion criteria | | ALL |
| --- | --- | --- |
| Women | - Age: 15-49 years - Confirmed pregnancy through clinical assessment or pregnancy test - Documented HIV-negative sero-status at the time of screening - Intention to breastfeed | a) Absence of serious medical condition  b) Willingness to be tested and counseled for HIV and other STIs  c) Residing within a 30 km radius around the study clinic and not planning on moving (*to be checked using place of origin, date of arrival and residence of relatives to reduce the possibility of selective attrition*);  d) Agreeing to come the study clinic for scheduled appointments and to be called by phone or visited at home as needed during follow up  e) Agreeing to provide written informed consent |
| Partners | - Age: >15 years - Recognized by an eligible pregnant woman as her current husband/partner for at least 6 months |

### C.4.3 Exclusion criteria

Women and their partners will be excluded for the following reason:

- Inability to provide informed consent
- Concurrent participation in a randomized trial or research study
- Social or other circumstances which would hinder follow-up during the study in the opinion of the site investigator

### C.4.4 Informed consent

Participants will be asked to provide written consent for the collection of blood, urine and vaginal/urethral swabs for HIV and STI testing, collection of personal data through questionnaires, group discussions and key informant interviews at baseline and follow-up visits, data abstraction from their medical records, and future use of biological specimens obtained during the study. Study counselors will conduct the consent discussion in the appropriate language and a translator will be used if necessary. Both members of couples will be consented together unless either partner opts to be consented individually. Printed consent forms translated in the language of participants and approved by the UCSF Committee for Human Research (CHR), Makerere University School of Medicine Research and Ethics Committee (SOMREC), and the Uganda National Council for Science and Technology (UNCST) will be used to describe the study to potential participants. Following the consent discussion, participants will be asked to sign the consent forms. Participants unable to read or write will use fingerprints in lieu of signature, and a signature will be obtained from a witness to confirm the consent process.

### C.4.5 Enrolment procedures

Consented women and men will be retested for HIV by rapid test. Women with an HIV-positive or indeterminate result will be ineligible for the study and referred back to the PMTCT clinic. Only women with a confirmed HIV-negative result will be enrolled either alone or with their partner, independent of the partner’s HIV serostatus. All newly enrolled participants will be counseled per the study counseling protocol. Both members of couples will be counseled together unless either partner opts to be counseled individually. In case of HIV serodiscordance, the infected partner will be bled after counseling for CD4 testing and referred to the HIV clinic for registration and ART eligibility assessment, if not already done. All participants will undergo a standard clinical examination by the study clinician. All women will be bled for syphilis testing and hemoglobin measurement, and a vaginal swab will be collected for gonorrhea/ chlamydia (G/C) and Trichomonas vaginalis (Tv) testing and to test for the presence of semen (Y chromosome). Men will also be tested for syphilis and a urine sample or urethral swab will be obtained for G/C and Tv testing. All enrolled women and partners will be asked to answer a baseline demographics and behavioral questionnaire about their socio-economic status (SES), sexual and relational behaviors, and reproductive history and intentions, including family planning. All interviews will be conducted in the language of participants. Questionnaires will be translated and back-translated to ensure consistency, accuracy and clarity of the questions.

### C.4.6 Randomization

There are four study arms:

| Individual Arm 1 (Arm I-1) | HIV-negative pregnant women enrolling **without** their partner and who will receive standard HIV retesting and counseling in late pregnancy only |
| --- | --- |
| Individual Arm 2 (Arm I-2) | HIV-negative pregnant women enrolling **without** their partner and who will receive the ERHTEC intervention in late pregnancy AND throughout breastfeeding as described below (C.5 Follow-up) |
| Couple Arm 1  (Arm C-1) | HIV-negative pregnant women enrolling **with** their partner and who will receive standard HIV retesting and counseling in late pregnancy only |
| Couple Arm 2 (Arm C-2) | HIV-negative pregnant women enrolling **with** their partner and who will receive the ERHTEC intervention in late pregnancy AND throughout breastfeeding as described below (C.5 Follow-up) |

Enrolled women and couples will be randomized to either the control (repeat HTC in late pregnancy [>36 weeks] only), or to the ERHTEC intervention. Prior to the study onset, four sets of randomized, sequentially numbered lists of participants identification numbers (IDs) will be prepared by the statistician at UCSF. The randomization lists will be computer-generated using random-sized block groups and will include consecutive intervention numbers with corresponding random intervention assignments. Randomization lists will be encrypted in password-protected files, backed up on computer and the UCSF server and emailed to the MU-JHU Data Center in Kampala. Sealed copies of the original randomization list and documentation of the procedure used to generate the lists will be stored in the project administrative offices in San Francisco and Kampala. Each enrolment number will be preceded with a code letter indicating the trial group (“I” for individual, “F” for the female partner of a couple, “M” for the male partner of a couple) and followed by a randomization allocation code (“E” for ERHTEC intervention, “C” for control) and a site code (“KA” for Kampala, “KI” for Kitgum).. At randomization, MU-JHU Data Center will issue randomization numbers to the study coordinators based on the order of enrollment at each site and on the participants’ group allocation (individual or couple).

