**C.7 Measures**

**C.7.1 Primary outcomes**

The primary outcomes are the frequency of unprotected sex and the incidences of HIV and STI over follow-up. The trial is powered to detect a 10% difference in the frequency of unprotected sex[[2]](#footnote-3) accounting for a 50% loss to follow-up over 2 years. The frequency of unprotected sex will be determined as the self-reported number of episodes of unprotected vaginal intercourse with inconsistent or no condom use in the last 3 months and will be validated by Y chromosome detection in vaginal swabs. Reports by each partner in the couple trial will be treated as two correlated outcomes.

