All data clerks and managers will have received training on the requirements of strict confidentiality regarding patient identifying information, and laptop security. To protect detailed health and personal information data, study record keeping and access to participant identifying information will follow strict written SOPs and data will be subjected to a variety of quality control procedures. All records will be kept on password protected computers at MU-JHU and UCSF. Participants will be identified primarily by their study number. All CRFs and identifiers will be kept in individual files in secured, access-limited rooms at the sites. Participant names and addresses will be stripped from the database prior to analysis. No individual identifier will be used in any reports or publications resulting from the study. Study investigators and coordinators will continuously mentor and monitor staff to ensure these procedures are followed according to SOPs in order to ensure data quality and confidentiality.

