# D. HUMAN SUBJECTS PROTECTION

## D.1 Ethical and regulatory considerations

The study will be conducted in compliance with country specific laws and regulatory requirements. The conduct of the study will also adhere to the GCP principles laid out by the International Conference on Harmonization (ICH) and the Declaration of Helsinki

The protocol and informed consent form will be reviewed and approved by the local IRB in Uganda, UNCST and at UCSF prior to enrollment or carrying out any study procedures. The PI will keep the IRB informed of the progress of the study on a regular basis including any unexpected untoward events, at minimum once a year according to the IRB requirements.

Written informed consent will be obtained from the study participants prior to any protocol-specified procedures being conducted.

To maintain confidentiality, unique study participant identification numbers will be used to identify the subject’s laboratory specimens, source documents, CRF, study reports, etc. All study records will be maintained in a secured location and consents and other identifying information will be kept in a locked cabinet in a room with restricted access which is locked during non business hours.

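### The enrolment number carries the arm letter, and the swabs meant to validate the self-reported powered outcome have no stated validation rule or comparison by arm

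*Protocol*

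**What the plan says.** **Identifier.** Protocol C.4.6 says the enrolment number starts with a letter for the trial group, is "followed by a randomization allocation code" (E for ERHTEC, C for control), and also carries a site code. D.1 says that "unique study participant identification numbers will be used to identify" the "laboratory specimens, source documents, CRF, study reports" of each subject. C.8.7 adds: "Participants will be identified primarily by their study number". No second, arm-neutral number is described, and no masking of interviewers, laboratory or data staff is stated.

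**Outcome.** C.7.1 names unprotected-sex frequency, HIV incidence and STI incidence as primary, and powers the trial on the first. That is a self-reported count over 3 months, which "will be validated by Y chromosome detection in vaginal swabs"; C.1 says the same for women. C.8.2 and C.8.3 give models for reported counts, STI, HIV, pregnancy, MTCT and mediators, but none for the swab result.

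**Baseline.** C.4.1 says: "Enrolled women/couples will be given an appointment to return within the next 2 weeks to complete baseline exams, tests and procedures". C.4.6 issues numbers by order of enrolment. C.4.5 mentions counseling before the swabs and questionnaire. Appendix C lists the swab and questionnaire first, then enhanced counseling for the intervention arm.

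**The concern.** There are three separate weaknesses.

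1. An ID that ends in the arm letter unmasks staff who have no need to know the arm.
2. The intervention arm is counseled on risk reduction at every visit and then asked how often it had unprotected sex. Extra under-reporting in that arm would look the same as a change in behavior. The protocol names an objective safeguard and collects it from all women at every assessment visit, but gives it no role in the comparison of arms.
3. The primary model estimates the effect as arm by follow-up versus baseline. A baseline report given after the participant knows the arm would enter that estimate directly, in either direction.

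At stake is whether a significant result can be read as behavior change. C.8.4 also feeds reported and validated behavior into the estimate of infections averted, so a reporting bias would carry into cost-effectiveness.

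**Working it through.** **Step 1: reproduce the stated power.** Inputs from C.8.5: 410 women alone and 410 couples, randomized 1:1; 7 assessments including baseline; baseline mean 5; control-arm reduction 30%; effect 10%; over-dispersion 2; correlation 0.3; 50% cumulative loss; two-sided 5%. Following C.8.5, the covariance is the inverse of the sum of X'WX, with a log link, variance 2 × mean, compound symmetry, two rows per visit for couples, and terms for visit, arm and arm by follow-up. C.8.5 does not fix the timing of dropout, so three patterns were tried.

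| Dropout pattern to 50% | SE of log ratio | Power |
|---|---|---|
| Constant rate | 0.0374 | 80.3% |
| Linear | 0.0369 | 81.4% |
| Linear, complete one visit earlier | 0.0375 | 80.2% |

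The stated 80% is reproduced. The target is 5 × 0.7 = 3.50 against 3.50 × 0.9 = 3.15 episodes, a gap of 0.35 per 3 months. With SE 0.0374, the result is significant once the observed ratio falls to about exp(−1.96 × 0.0374) = 0.93.

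**Step 2: no true effect, extra under-reporting d in the intervention arm.** The expected log ratio is ln(1 − d). Rejection probability = Φ(|ln(1 − d)|/SE − 1.96) + Φ(−|ln(1 − d)|/SE − 1.96). Results for the constant-rate pattern, with the SE re-evaluated at each ratio (0.0371 to 0.0374):

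| d | \|ln(1 − d)\| | Chance of significance |
|---|---|---|
| 10% | 0.1054 | 80% |
| 5% | 0.0513 | 28% |
| 3% | 0.0305 | 13% |
| 0 | 0 | 5% (2.5% in the favorable direction) |

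**Step 3: can the biological primary outcomes expose this?** The protocol's footnote on power puts the required sample above 2,500 for a 30% reduction in HIV or STI incidence, and above 1,500 for a composite STI endpoint. With 410 women per arm, no dropout, and an assumed 2-year cumulative incidence of 4%, 8% or 12%, power for a 10% reduction is about 5%, 6% or 8%. For a 30% reduction it is 16%, 28% or 40%. They cannot.

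**Step 4: what could a swab comparison do?** There are 205 + 205 = 410 women per arm and six follow-up assessments. Under constant-rate dropout, swabs per woman = sum of 0.5^(v/6) for v = 1 to 6 = 4.08. Design effect at correlation 0.3 = 1 + 3.08 × 0.3 = 1.92. Effective number per arm = 410 × 4.08/1.92, about 870. Positivity is not given in the protocol, so a range is assumed.

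| Assumed control positivity | 10% | 20% | 30% | 40% | 50% |
|---|---|---|---|---|---|
| Power, 10% relative difference, correlation 0.3 | 11% | 19% | 28% | 40% | 55% |

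At correlation 0.1, power runs from 14% to 72%. Converting power to a mean z-value (1.96 + Φ⁻¹(power)), a true 10% effect would point the wrong way about 24%, 14% and 8% of the time at 10%, 20% and 30% positivity. With no true effect, the swab would agree in direction about half the time.

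**The case against.** **The code does not cause the reporting bias.** Participants and counselors know the arm from the counseling and the visit schedule. A reader might infer that the arm letter lets a 10% reporting difference pass as an effect. The documents do not support that link, because removing the letter would leave participant reporting unchanged. This stands, and the two matters are kept apart here.

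**Not all testing can be masked.** C.3.3 trains the study counselors to perform the rapid HIV, STI and pregnancy tests. Neutral labels help only staff outside counseling. This stands.

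**The label is an inference.** C.4.6, C.8.7 and D.1 use several terms for the number, and none says that the full string goes on specimens. It is the plain reading, since C.4.6 describes the lists as lists of participant IDs, but it is still an inference.

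**Baseline contamination is not shown.** A reader might infer that the two-week return visit falls after allocation is known. Order of enrolment fixes the sequence of numbers, not the time of disclosure, and Appendix C lists the swab and questionnaire before enhanced counseling. The order is left open, so contamination is possible and no more.

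**Objective primary outcomes exist and are compared by arm.** True, but Step 3 shows that they are too weak to serve as a check.

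**A statistical analysis plan may hold the swab analysis.** Possible. The point is limited to what the protocol fixes: it promises validation and details its other models, but states no rule for this one.

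**Step 2 is nearly circular.** A trial with 80% power for a 10% effect will flag a 10% bias about as often. Agreed: the sizes are illustrative, and nothing in the protocol measures the bias.

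**Conclusion.** The concern holds in limited form. The arm letter in the ID is avoidable unmasking of non-counseling staff, given the inference that the enrolment number is the one used on records. No resulting bias in laboratory readings is quantified. Separately, the powered outcome is unmasked self-report, and its named safeguard has no stated rule or comparison by arm. If the intervention arm under-reports by 10%, 5% or 3% more than control and the true effect is nil, significance follows in about 80%, 28% or 13% of trials (SE about 0.037, C.8.5 inputs). The order of baseline measures and allocation is unspecified. The stated sample size and power are not in error.

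A reader might also infer that a claim of behavior change should require the swab to agree in direction. The figures in Step 4 do not support that. Such a rule would block real effects too often and would pass about half of null trials. It also could not cover the 410 men whose reports enter the primary model.

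**What to change.** 1. Take the E/C letter out of the ID. Hold allocation in the Data Center list and use arm-neutral labels on specimens and outcome case record forms.
2. State that allocation is released only after the baseline questionnaire and swabs are complete, and align C.4.1, C.4.5, C.4.6 and Appendix C.
3. Pre-specify, as supportive analyses with confidence intervals, comparisons by arm of (a) Y-chromosome positivity in women at the visits common to both arms and (b) swab positivity among women reporting no unprotected sex. Do not make the direction of either result a condition for the primary conclusion.

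The cost is a change of ID format, a fixed order of steps at baseline, and one added set of analyses of swabs already collected. There is no new procedure and no change in sample size.

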## C.5 Follow-up

### C.5.1 Repeat HTC in late pregnancy (>36 weeks)

All women will be given an appointment to be retested and counseled for HIV in late pregnancy as per WHO and Uganda MOH recommendations. Women enrolled at or before the 16th gestational week will be given an appointment for ERHTEC or repeat HTC at 28 weeks of gestation. Women enrolled after the 16th up to the 32nd gestational week will be given an appointment for ERHTEC or repeat HTC at 36 weeks of gestation, or at the first signs of labor, whichever comes first. Women enrolled between the 32nd and 36th gestational week will be given an appointment for ERHTEC or repeat HTC 6 weeks later or at the first signs of labor, whichever comes first. Women enrolled after the 36th gestational week will be given an appointment for repeat HTC at the 6-week post-partum visit to coincide with the first routine immunization visit. In the event that a pregnant woman or couple does not return on the scheduled appointment but presents for delivery, she/they will be retested immediately before or after delivery as per the WHO recommendation. At the late pregnancy retesting visit, all women and men randomized to the intervention arms (Individual and Couple Arms ‘2’) will receive the ERHTEC intervention while women and men randomized to the control arms (Individual and Couple Arms ‘1’) will receive standard HIV retesting and counseling. In addition, both intervention and control women will be bled for syphilis testing and hemoglobin measurement and a vaginal swab will be collected for testing for Gonorrhea/ Chlamydia (G/C), Trichomonas vaginalis (Tv) and the presence of semen (Y chromosome). Symptomatic men will be bled for syphilis testing and asked for a urine sample or urethral swab for G/C and Tv testing. All enrolled women and couples will be asked to answer a follow-up behavioral questionnaire about their sexual and relational behaviors, and reproductive intentions, including family planning. All interviews will be conducted in the language of the participants.

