**205 women receive ERHTEC in late pregnancy + at 3,6,12, & 18 mos post-partum**

**205 couples receive repeat HTC in late pregnancy**

**205 couples receive ERHTEC in late pregnancy + at 3,6,12, & 18 mos post-partum**

**Arm I*-1**

**Arm I*-2**

**Arm C*-1**

**Arm C*-2**

**** I = Individual; C = Couple***

Follow-up will end at 24 months postpartum or 6 weeks after the end of breastfeeding, whichever occurs first. Quantitative data will be collected on participants’ HIV and STI status, socio-demographics characteristics, risk behaviors and perceptions, as well as relational factors and reproductive history and intentions. The primary outcomes will be the frequency of unprotected sex and the incidences of HIV and STI over follow-up. Self-reports of unprotected sex by women participants will be validated by testing women for the presence of semen biomarkers (Y chromosome) in vaginal swabs[36](#_ENREF_36). We will also collect qualitative data at baseline and at the end of follow-up on the knowledge, perceptions and experiences of study participants and providers on the challenges of retesting, partner’s involvement and primary HIV prevention.

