**C.5.2 Postpartum intervention schedule and assessments**

After the late pregnancy visit, all women and couples in the intervention arm will be asked to return at 6 weeks and 3 months postpartum and every 3 months thereafter until the end of follow-up at 24 months postpartum or 6 weeks after the end of breastfeeding, whichever occurs first. Women and couples in the control arm will be asked to return at 3 and 6 months postpartum and every 6 months thereafter until the end of follow-up at 24 months postpartum or 6 weeks after the end of breastfeeding, whichever occurs first.

Participants randomized to the intervention arms (Arms I-2 & C-2) will receive enhanced counseling at every visit and will be retested for HIV at 3, 6, 12, 18 and 24 months postpartum (or at the end of follow-up, whichever occurs first). At these visits, both intervention and control women and men participants will undergo a physical examination and will be asked to answer individually a follow-up behavioral questionnaire about their sexual behaviors, relational and reproductive intentions, including family planning. At these same visits, all women will be bled for syphilis and HIV rapid testing and two vaginal swabs will be collected, one for G/C, and Tv testing and the other for Y chromosome detection while a blood or urine sample or urethral swab will be obtained from symptomatic men for syphilis, G/C and Tv testing [*See Schedule of Events, Appendix C*].

At the end of follow-up, all study participants irrespective of their arm assignment will undergo a physical examination, will be asked to answer individually an end-of-study questionnaire and will be bled for syphilis and HIV rapid testing and a vaginal or urethral swab will be collected for G/C and Tv testing. A vaginal swab will also be collected from women to test for the presence of Y chromosomes.

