
**C.8.4 Cost and cost-effectiveness**

We will assess the cost of individual and couple-based testing based on the current WHO and our repeat HTC schedule. We will measure the total cost, cost-per-site and cost-per-patient for the intervention and the comparison arms. We will compare the cost of individual and couple-based repeat HTC for both the current WHO recommendation as well as the ERHTEC intervention. We will estimate the cost-effectiveness of repeat HTC by estimating the number of HIV infections averted through these interventions using previously described methods. We will estimate the probability of HIV acquisition for each woman at each time point based on self-reported and validated sexual behavior, HIV and ART status of a woman’s partner and community prevalence of HIV. We will then compare the effectiveness and cost-effectiveness of both individual and couple-based repeat HTC to the controls.

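### Y-chromosome detection is read as semen at pregnancy visits too, where a male fetus is another possible source, so the marker's specificity there is unknown

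*Protocol*

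**What the plan says.** C.1 Study Design gives the marker its role: "Self-reports of unprotected sex by women participants will be validated by testing women for the presence of semen biomarkers (Y chromosome) in vaginal swabs". C.7.1 repeats this for the primary behavioral outcome, a self-reported count of episodes over the last 3 months.

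The swabs are scheduled as follows:

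- **Baseline (C.4.5).** All women are pregnant. A vaginal swab is taken for STI testing and "to test for the presence of semen (Y chromosome").
- **Late pregnancy (C.5.1).** In both arms, "a vaginal swab will be collected for testing for Gonorrhea/ Chlamydia (G/C), Trichomonas vaginalis (Tv) and the presence of semen (Y chromosome"). Women enrolled by week 16 come at 28 weeks. Those enrolled after week 16 and up to week 36 come at 36 weeks or 6 weeks after enrolment, "or at the first signs of labor, whichever comes first". A woman who misses the appointment but presents for delivery falls under this rule: "she/they will be retested immediately before or after delivery as per the WHO recommendation". "Women enrolled after the 36th gestational week will be given an appointment for repeat HTC at the 6-week post-partum visit", so for them only the baseline swab is certain to fall in pregnancy.
- **Postpartum (C.5.2).** At 3, 6, 12, 18 and 24 months, "two vaginal swabs will be collected, one for G/C, and Tv testing and the other for Y chromosome detection".

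C.8.4 estimates each woman's probability of acquiring HIV at each time point "based on self-reported and validated sexual behavior", together with the partner's HIV and ART status and community prevalence.

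No section mentions fetal sex, fetal DNA, a separate reading rule for pregnancy or delivery swabs, or the sensitivity or specificity of the test.

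**The concern.** The marker indicates semen only if semen is the only source of Y DNA in the swab. In a woman carrying a boy it need not be, and the possibility is plainest around delivery, when fluid, cells and blood of fetal origin can pass through the vagina. A woman who truthfully reports no unprotected sex could then be Y-positive, and the protocol's rule would take that as disagreement with her report.

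The powered outcome rests on self-report, and the second footnote explains that the trial could not be powered on HIV or STI incidence. The Y marker is the stated objective check on those counts. If its specificity is lower in pregnancy than postpartum, reporting will seem to become more truthful after birth although nobody's behavior or candor has changed. C.8.4 works time point by time point, so the pregnancy visits could carry the same error into the estimate of infections averted.

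**Working it through.** **1. The plan's own figure.** The protocol gives no accuracy figure for the marker. The nearest stated figure is the 80% power in C.8.5. Its inputs are 410 women and 410 couples, 7 assessments, correlation 0.3, over-dispersion 2, baseline mean 5, control-arm reduction 30%, effect 10%, 50% dropout and two-sided 5%. The X'WX method described there gives a standard error for the log rate ratio of 0.03692 with linear dropout and 0.03744 with geometric dropout. Power = Φ(|ln 0.9|/SE − 1.96):

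- linear: 0.1054/0.03692 − 1.96 = 0.89, power 81.4%
- geometric: 0.1054/0.03744 − 1.96 = 0.85, power 80.4%

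The stated 80% is reproduced. No term involves the swab result, so the concern leaves it unchanged.

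**2. How many assessments are concerned.** The seven are baseline, late pregnancy, and 3, 6, 12, 18 and 24 months. At most two fall in pregnancy or around delivery:

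- of scheduled assessments: 2/7 = 29%
- of attended assessments, if the 50% loss is linear: (12 + 11)/(12 + 11 + 10 + 9 + 8 + 7 + 6) = 23/63 = 37%
- the only baseline swab, but 1 of 6 follow-up swabs (17%)

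The last line matters most: the possible error is concentrated on the baseline side of any before/after comparison.

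**3. Size of the error.** Let m be the share of male fetuses and q the probability that a swab from a woman carrying a boy shows fetal Y DNA. Neither is in the documents. I assume m = 0.5 and vary q. Among women with no semen present, the false-positive rate is m × q. If a share π truly has semen present, false positives among all swabbed women are (1 − π) × m × q. With π = 0.6 (also an assumption):

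| q | No semen present: 0.5 × q | All women: 0.4 × 0.5 × q | Of 820 baseline swabs |
|---|---|---|---|
| 5% | 2.5% | 1% | 8 |
| 25% | 12.5% | 5% | 41 |
| 50% | 25% | 10% | 82 |
| 100% | 50% | 20% | 164 |

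At q = 0 there is no error. The value of q probably differs between an intact pregnancy and labor or delivery, so one figure need not serve both.

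**4. What this does to validation over time.** Take women who truthfully report no unprotected sex. With q = 25%, 12.5% of them would be Y-positive in pregnancy from the fetal source, and none postpartum unless pregnant again. Apparent under-reporting would fall by 12.5 points with no change in reporting.

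**The case against.** The strongest reply is that little depends on this marker. C.8.2 compares counts as reported by participants, men included, and no section uses the Y result to correct or replace a count. Fetal sex is independent of randomized arm and both arms are swabbed at the same scheduled visits, so an antenatal error should be balanced between arms. That stands.

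A reader might infer that the marker is false-positive in up to half of the women swabbed in pregnancy. The documents do not support this. Half is reached only if every male pregnancy yields a positive swab, and then only among women with no semen present. Nor do they support calling the assay PCR, which the protocol names only for infant HIV testing. A swab right after delivery is also implied rather than stated, because the fallback sentence speaks of retesting. The first signs of labor, by contrast, are explicit.

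It can also be said that reading an ancillary marker belongs in a laboratory procedure or analysis plan. That is true of the statistics. It is less true of recording infant sex and whether a swab was taken in labor, which may not be recoverable unless planned at collection.

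One limit applies to the claim of balance. Postpartum swabs are exposed again if a woman becomes pregnant. The intervention includes family planning counseling, and recurrent pregnancy is compared between arms as a secondary outcome. Balance on postpartum swabs therefore cannot be taken for granted, although no imbalance is shown.

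**Conclusion.** The point holds in limited form. The protocol treats Y chromosome as evidence of semen at every visit and has no provision for a male fetus at baseline or late pregnancy, at most 2 of 7 assessments. Specificity there is unknown and may differ from that at postpartum visits. The false-positive rate among women with no semen present runs from 0 to 50% over the whole range of q, given m = 0.5. The documents do not narrow that range.

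The effect is confined to the validation of self-report over time and to the validated behavior entering C.8.4, and C.8.4 does not say how the marker enters. The primary estimate and its 80% power are untouched, and no bias between arms from the antenatal swabs is shown. This is a cheap improvement to a supporting measure.

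**What to change.** In C.5.1 and C.7.1:

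1. Exclude swabs taken in labor or around delivery from Y-chromosome validation, and record at collection whether a swab was so taken.
2. Base the main validation, and the marker's contribution to C.8.4, on scheduled postpartum swabs from women not pregnant again. C.7.2 already provides for diagnosing new pregnancies.
3. Record infant sex at birth, and report baseline and pre-labor antenatal Y results separately by infant sex. The difference in Y-positivity between mothers of boys and mothers of girls is a direct check on the fetal contribution.

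The cost is some wording, one recorded variable and one stratified table, with no new samples. The downside is that fewer antenatal swabs count toward the main validation: 5 of 7 scheduled assessments remain (71%), and baseline reporting is checked only through the split by infant sex. Restricting to women not pregnant again also conditions on an event after randomization. That is acceptable for describing agreement between marker and report, but any comparison of agreement between arms should carry that caveat.
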